#### Machine learning

##### Preprocessing and feature selection

Given the multimodal nature of the BIOMIGA dataset and the high dimensionality arising from the integration of clinical, psychometric, biomolecular, genetic, epigenetic and neuroimaging variables, a structured preprocessing and feature-selection pipeline are going to be implemented to reduce dimensionality, limit multicollinearity and minimise the risk of overfitting.

Continuous variables are going to be inspected for distributional properties and standardised when appropriate. Categorical variables are going to be encoded using dummy variables. Pairwise correlation analysis is going to be performed to identify highly collinear features, and redundant variables will be excluded before model training.

An initial univariate feature-screening step is going to be applied to reduce the feature space. Candidate predictors is going to be tested for their association with the target variable (treatment response category) using appropriate statistical tests (*t*-test or ANOVA for continuous variables; *χ*^2^ test for categorical variables). Variables not showing evidence of association is going to be excluded from subsequent modelling. This step is going to be used exclusively for dimensionality reduction and not for inferential purposes.

To prevent information leakage, all preprocessing and feature-selection steps is going to be performed within the training data only, following best practices for predictive modelling. Given the protocol-oriented nature of the present manuscript and the proof-of-concept design of BIOMIGA, the machine-learning analyses are planned as an exploratory predictive modelling component intended to generate and prioritise candidate multimodal predictors of treatment response, rather than to provide a definitive externally validated clinical prediction tool.

##### Handling of class imbalance

Given the expected imbalance between response categories (e.g., super-responders, responders, partial responders and non-responders), class imbalance is going to be explicitly addressed during model training. For Random Forest (RF) models, class imbalance is going to be handled by applying class-weighted training, assigning higher misclassification penalties to underrepresented classes. For algorithms requiring explicit balancing, resampling strategies within the training folds is going to be considered while preserving the original class distribution in the test data. Model performance is therefore going to be evaluated using metrics that are robust to class imbalance, rather than relying solely on overall accuracy.

##### Machine learning (ML) algorithms

As the primary modelling approach, RF classification was selected because it is well suited to high-dimensional biomedical datasets, can model non-linear relationships and interactions among predictors, and provides internal estimates of generalisation error through out-of-bag (OOB) samples. RF models is going to be trained using bootstrap aggregation, with random feature selection at each node split. Hyperparameter tuning will consider the number of trees, the number of variables sampled at each split, tree depth and terminal node size; final values are going to be selected according to cross-validated/OOB performance. RF-derived feature-importance measures are going to be used to rank predictors according to their contribution to classification performance. This approach is consistent with recent migraine studies using ML to predict response to anti-CGRP monoclonal antibodies (26, 28).

To assess the incremental predictive value of multimodal data integration, RF models are going to be developed using a progressive feature expansion strategy. Models are going to be trained and compared using: (i) clinical and biochemical variables; (ii) clinical, biochemical, and genetic variables; (iii) clinical, biochemical, genetic, and epigenetic variables; (iv) clinical, biochemical, genetic, epigenetic, and structural MRI variables; and (v) the full multimodal dataset including clinical, biochemical, genetic, epigenetic, structural MRI, and functional MRI (fMRI) features. This sequential approach will quantify the added predictive contribution of each data modality and reduce the likelihood that model performance is driven by a single data source or modality-specific confounding effect.

Following this initial phase, a stricter feature-selection step based on RF importance rankings is going to be applied to identify a reduced and more informative feature subset. This reduced feature space will then be used to train and compare additional supervised machine-learning algorithms, including:Support vector machine (SVM): Linear and radial-basis-function kernels are going to be considered to test whether response categories can be separated by maximum-margin decision boundaries in the selected feature space. The regularisation parameter and, for radial-basis-function kernels, the gamma parameter is going to be tuned within the inner validation loop. SVMs have previously been applied to migraine classification using clinical and neuroimaging-derived variables (40).Artificial neural network (ANN): simple feed-forward multilayer perceptron models are going to be considered to capture potential non-linear relationships among multimodal predictors. Given the limited sample size, the ANN architecture is going to be intentionally parsimonious, with tuning of the number of hidden units/layers, regularisation strength and learning rate, and with early stopping where appropriate to reduce overfitting. Neural-network approaches are included as exploratory non-linear benchmark models in line with the broader use of artificial intelligence methods in migraine research (29).k-Nearest Neighbour (kNN): Distance-based classification is going to be applied after appropriate scaling of continuous predictors. The number of neighbours and distance metric are going to be selected within the training folds. kNN will serve as a simple, non-parametric benchmark model that classifies subjects according to similarity with neighbouring cases in the reduced multidimensional biomarker space (41)Decision Tree: classification-tree models are going to be used as interpretable non-linear classifiers able to represent threshold-based combinations of predictors. Tree depth, minimum node size and pruning/complexity parameters are going to be tuned to limit overfitting. Decision-tree models will also provide a clinically intuitive comparator to ensemble methods such as RF and AdaBoost (40)AdaBoost: adaptive boosting models based on weak decision-tree learners are going to be considered to assess whether sequential reweighting of misclassified observations improves classification. The number of estimators, learning rate and base-tree complexity are going to be are going to be tuned within the inner validation loop. Boosting approaches, including AdaBoost, have previously been used in migraine classification studies combining questionnaire and imaging-derived variables (40, 42, 43, 54).

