The biomarkers selected for the BIOMIGA study reflect a unified pathophysiological rationale, and each domain detects a complementary level of CGRP-mediated trigeminal-vascular activation. Peripheral neuroinflammatory signalling is associated with circulating levels of CGRP and cytokines, which reflect the degree of trigeminal activation at the time of treatment. Individual biological susceptibility to dysregulation of CGRP signalling is assessed through genetic variants and DNA methylation profiles at loci within the CGRP pathway. Central network reorganisation, a downstream consequence of prolonged trigeminal-vascular input, is quantified through resting-state functional connectivity. Together, these converging signals at all levels, rather than a single marker, are expected to predict response to erenumab. The resulting predictive models is expected to guide treatment decisions in patients with severe disability, such as those with CM, and provide essential evidence to healthcare systems and payers to support the rational and equitable allocation of advanced therapies.

We therefore hypothesise that the assessment of a wide panel of migraine-relevant features will yield a composite biomarker profile capable of predicting the response to treatment with anti-CGRP mABs in migraine prevention.

To address this hypothesis, BIOMIGA (BIOmarkers of MIGraine) project (Figure 1) was designed as a proof-of-concept multidisciplinary study with the following specific objectives:To define the clinical and omics differences between subjects with migraine stratified according to their response (responders vs. non-responders) to treatment with a CGRP-targeting mAb;To identify a predictive profile using advanced machine learning techniques to analyze the integrated clinical and omics database generated from responder and non-responder data;To integrate the findings from human studies with the evaluation of CGRP-targeting drugs in validated animal models of migraine.

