#### Handling missing data

Missing values in clinical and psychometric variables (BAI, BDI-II, MIDAS, HIT-6, MSQ total score), as well as missing body mass index (BMI) values, were handled using multiple imputation by chained equations (MICE) implemented in R (2), based on Fully Conditional Specification, whereby each incomplete variable was imputed using a separate regression model appropriate to its distribution. Regarding neuroimaging data, missing or incomplete MRI datasets were not imputed. Across centres, minor differences in acquisition resulted in variable numbers of volumes, particularly in resting-state fMRI sequences. To ensure comparability across sites, resting-state datasets were temporally harmonised by retaining an equivalent number of volumes for all subjects included in the analyses.

In addition, datasets affected by excessive head motion, defined as motion artefacts that could not be adequately corrected using standard motion-correction algorithms during preprocessing, were excluded from neuroimaging analyses. This quality-control step was applied uniformly across centres to minimise motion-related bias and to preserve the validity of functional connectivity and perfusion measures.

No imputation was performed for missing neuroimaging data; analyses were conducted on quality-controlled datasets only.

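### The model ladder starts at clinical plus biochemical variables, so it gives no increment for the biochemical block and no clinical-only reference, although it is said to quantify what each modality adds

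*Protocol article*

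**What the plan says.** The section Machine learning (ML) algorithms sets out a progressive expansion of random forest models. The first two rungs are given as "Models are going to be trained and compared using: (i) clinical and biochemical variables; (ii) clinical, biochemical, and genetic variables". The third adds epigenetic variables, the fourth structural MRI, and the fifth is "the full multimodal dataset including clinical, biochemical, genetic, epigenetic, structural MRI, and functional MRI (fMRI) features". The purpose is stated directly: "This sequential approach will quantify the added predictive contribution of each data modality".

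The Background treats the biochemical measures as a biomarker domain in their own right, one of several complementary levels of the hypothesis: "Peripheral neuroinflammatory signalling is associated with circulating levels of CGRP and cytokines".

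Under Handling missing data, multiple imputation is described for BAI, BDI-II, MIDAS, HIT-6, MSQ and body mass index. For imaging, "Regarding neuroimaging data, missing or incomplete MRI datasets were not imputed", and scans with uncorrectable motion "were excluded from neuroimaging analyses". The section closes: "No imputation was performed for missing neuroimaging data; analyses were conducted on quality-controlled datasets only". It does not give the analysis set for any rung of the ladder.

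**The concern.** A nested ladder measures what a block adds only where two adjacent rungs differ by that block alone. Here the lowest rung already joins clinical and biochemical variables, so no pair of models differs by the biochemical block. The article enumerates the models and also says what they are for, and the enumeration cannot deliver the purpose for one of the modalities. This is therefore a mismatch within the text, and not a detail left to a fuller document.

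Two things are at stake. First, circulating CGRP, which the Limitations describe as having been proposed as the most promising candidate marker, would have no reported increment in predictive performance. Second, without a clinical-only reference the ladder cannot show what the whole biomarker panel adds to information a clinic already holds. The Background expects the models to inform treatment decisions and payers, and that question matters to both.

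A secondary issue is conditional. If patients without usable MRI are kept in steps (i) to (iii) and drop out of (iv) and (v), the difference between (iii) and (iv) mixes new features with a changed patient set.

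**Working it through.** **1. Rungs and contrasts.** The plan states no figure here, so there is none to reproduce. Setting the models side by side:

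| Contrast | What it adds |
|---|---|
| (ii) − (i) | genetic |
| (iii) − (ii) | epigenetic |
| (iv) − (iii) | structural MRI |
| (v) − (iv) | functional MRI |
| none | biochemical |
| none | all biomarkers over clinical data |

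The top rung holds six blocks. Taking clinical data as the base leaves five blocks to be added, but five models give only 5 − 1 = 4 contrasts. No clinical-only model appears in Efficacy endpoint analyses, in Descriptive and inferential statistics, or in the sections from there to Model evaluation and validation. With a step (0) there are six models and 6 − 1 = 5 contrasts, one per biomarker block, and (v) − (0) gives the panel as a whole.

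**2. What the missing rung hides (illustration).** Assume a step (i) AUC of 0.70 and independent, normally distributed clinical and biochemical scores. Then AUC = Φ(d/√2), and squared separations add. Φ⁻¹(0.70) = 0.524. If biochemistry carries a share s of the squared separation, the clinical-only AUC is Φ(0.524 × √(1 − s)):

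- s = 0: 0.70
- s = 0.25: Φ(0.454) = 0.675
- s = 0.50: Φ(0.371) = 0.645
- s = 1: Φ(0) = 0.50

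The planned ladder shows the same 0.70 in all four cases.

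**3. Size of a patient-set effect, if the sets differ.** The documents give no rate of unusable MRI, so everything here is assumed.

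*Selective loss.* Baseline headache days are uniform over 8 to 25, and response is logistic in headache days with slope 0.15 or 0.20 per day. A fraction m of patients above 20 days lacks usable MRI. These patients are (25 − 20)/(25 − 8) = 29.4% of the cohort. The AUC of one unchanged clinical predictor moves as follows:

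| m | Share of cohort lost | Fall in AUC |
|---|---|---|
| 20% | 0.20 × 29.4% = 5.9% | about 0.005 |
| 30% | 0.30 × 29.4% = 8.8% | about 0.006 to 0.008 |
| 70% | 0.70 × 29.4% = 20.6% | about 0.025 to 0.03 |

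At 70% the AUC goes from 0.70 to 0.67 (slope 0.15) or from 0.75 to 0.72 (slope 0.20).

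*Random loss.* The planned 168 patients less 6% is 168 × 0.94 = 158. In 4,000 simulated cohorts with MRI carrying no information, the AUC in the MRI subset minus the AUC in all patients averaged about zero. Its 95% range was about ±0.03 at 10% loss, ±0.04 at 20%, and −0.05 to +0.06 at 30%.

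*Precision.* With A = 0.70 and an equal split of responders and non-responders, the Hanley–McNeil formula is SE² = [A(1 − A) + (n₁ − 1)(Q₁ − A²) + (n₀ − 1)(Q₂ − A²)]/(n₁n₀), where Q₁ = A/(2 − A) and Q₂ = 2A²/(1 + A). It gives 0.041 at n = 158 and 0.050 at n = 111 (30% loss).

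**The case against.** The strongest reply is that clinical plus biochemical may be the intended base, that the approach is openly sequential, and that the machine learning is repeatedly labelled exploratory. The primary objective is a panel associated with response, and superiority over clinical data is not claimed. This limits the consequence. It does not remove the mismatch, because the article promises the contribution of every modality and names circulating CGRP and cytokines as a domain under test.

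Several stronger readings are tempting, and the documents do not support them.

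- *The biochemical contribution is never examined.* Descriptive and inferential statistics plans logistic models for CGRP, IL-1β and TNF-α thresholds. Mitigation of confounding factors describes covariate-adjusted models for the CGRP cut-offs, and the random forest ranks predictors by importance. None of these is an increment in predictive performance, but they do examine the block.
- *The ladder quantifies no modality.* Four of the five increments exist as written.
- *The MRI steps will run on different patients, so the differences may have the wrong sign.* The text permits this but does not state it. Imputation is described only for the psychometric and disability scales and body mass index, so it does not follow that even steps (i) to (iii) use all patients. A common set could be fixed in a fuller document that is not shown.
- *Frequent-headache patients will lack scans.* Neuroimaging profiling says scans were rescheduled after an attack. The Limitations link the difficulty of finding pain-free days in chronic migraine to variability of measurements, not to absent scans. A 70% loss above 20 days is an extreme assumption.
- *A single order of entry is an error.* Increments conditional on order are what a sequential ladder reports, and alternative orders are a preference.

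**Conclusion.** The point holds in a limited form. As written, the ladder gives no increment in predictive performance for the biochemical block and no clinical-only reference, contrary to its stated purpose. This follows from the list of models alone and needs no assumption. The genetic, epigenetic, structural MRI and fMRI increments remain estimable, conditional on order of entry.

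How much the biochemical block contributes cannot be said in advance. The span of 0.50 to 0.70 for the clinical-only AUC rests on an assumed step (i) AUC of 0.70 and independent normal scores, and only shows that the planned output cannot distinguish these cases.

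The patient-set question is a safeguard and not an established flaw. The size of any case-mix shift is unknown; the fall of roughly 0.005 to 0.03 holds only under the assumed setup with 20% to 70% loss above 20 headache days.

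**What to change.** Add a random forest on clinical variables only as step (0) and report five contrasts, one each for biochemical, genetic, epigenetic, structural MRI and fMRI, plus the full model against step (0). If this is not wanted, narrow the sentence so that it claims only the four modalities the ladder covers.

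As a safeguard, state that adjacent steps are compared on the same patients and the same outer folds, and report the paired AUC difference with its interval. This sets to zero any part of the difference caused only by a change of patients. Give the all-patient result for steps (0) to (iii) as a sensitivity analysis.

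The first change costs one further model fit on data already collected; the narrower sentence costs nothing. The safeguard costs some refitting and leaves fewer patients in the early steps of the main comparison. Status of the study reports that processing for the stratified groups is still under way, so either change can be made before those results are reported.

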### Statistical analysis

#### Efficacy endpoint analyses

The primary objective of the study is to identify a panel of biomarkers that is reliably associated with response to treatment in a substantial proportion of patients with migraine. To this end, we will develop classification algorithms that assign patients to response categories defined on an ordinal scale. Supervised machine-learning approaches based on parametric, semi-parametric and non-parametric models are going to be fitted and compared. The optimal model will be selected according to predefined performance criteria, including area under the curve (AUC), accuracy, precision and recall.

Secondary analyses will characterise differences between migraine patients and healthy controls at baseline in: (i) DNA methylation profiles; (ii) structural and functional magnetic resonance imaging measures; and (iii) pharmacogenetic, biochemical, clinical and psychological variables. Within the migraine cohort, we will also compare DNA methylation, brain morphometry and functional connectivity, as well as pharmacogenetic, biochemical, clinical and psychological measures, among patients classified as responders and non-responders to CGRP-targeting mABs.

Given the prospective design, changes in clinical status, disability and psychometric measures, from baseline to the end of the treatment period, are going to be evaluated to quantify the impact of the therapy and to relate these changes to treatment response categories. In parallel, longitudinal differences in structural and functional magnetic resonance imaging measures among response groups are going to be examined to identify treatment-related brain changes and estimate their effect sizes in relation to drug exposure and clinical improvement (e.g., reduction in monthly headache days).

Finally, plasma concentrations of CGRP, IL-1β and TNF-*α*, together with their messenger RNA expression in peripheral blood mononuclear cells, are going to be assessed over the course of treatment to explore treatment-related alterations in peripheral inflammation and their correlation with clinical endpoints, including headache frequency, acute medication intake and disability.

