
#### Model evaluation and validation

These models are going to be evaluated within a nested cross-validation framework, with inner loops for hyperparameter tuning and outer loops for performance estimation, to ensure an unbiased assessment of generalisation performance. All transformations, feature-selection procedures, class-balancing strategies and hyperparameter optimisation steps are going to be confined to the training folds and then applied to the corresponding validation/test folds. For RF models, predictive performance will also be assessed using the out-of-bag (OOB) error rate, which provides an internal estimate of generalisation performance without the need for a separate validation set. OOB misclassification rates and class-specific OOB errors are going to be examined as global and category-specific performance indicators. For models evaluated using cross-validation, performance is going to be quantified using a combination of metrics, including balanced accuracy, sensitivity, specificity, positive and negative predictive values and area under the receiver operating characteristic curve (AUC), allowing comparison across algorithms in the presence of class imbalance.

This multi-step modelling strategy was designed to balance predictive performance, robustness and interpretability in the context of a complex, high-dimensional biomarker dataset. Because the final model specification depends on the observed data structure and on the retained feature set, the complete algorithmic configuration, selected hyperparameters and final validation results are going to be reported in the subsequent results manuscript. A schematic overview of the machine-learning pipeline, including preprocessing, feature selection, model training, validation and performance evaluation, is provided in Figure 3. This workflow illustrates the sequential and nested structure of the analysis and highlights the measures adopted to minimise overfitting and information leakage.

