### Strengths

A major strength of BIOMIGA is its prospective, multicentre design to collect extensive multimodal data in order to perform deep phenotyping of the patients. The collaboration of three specialised European headache centres, operating under harmonised protocols and shared standard operating procedures, increases sample size and enhances the external validity of the findings compared with single-centre series. The inclusion of patients living with HFEM and CM, often with several previous preventive failures, reflects real-world candidates for CGRP-targeting mABs and complements the more selected populations enrolled in pivotal randomised trials. Cross-centre quality checks and consensus procedures for resolving discrepancies further strengthen the reliability of the clinical and biomarker datasets.

Another key strength is the depth of phenotyping. BIOMIGA integrates detailed clinical and psychometric evaluations with peripheral biohumoral markers (e.g., CGRP, inflammatory cytokines, and their miRNA expression), genomic and epigenomic data (e.g., candidate SNPs and genome-wide DNA methylation), and advanced structural and functional magnetic resonance imaging. Unlike traditional databases, which handle only structured tabular data, the BIOMIGA database contains diverse data types, including text, images and specialised data such as genomic sequences. Managing the BIOMIGA dataset has presented challenges in terms of storing, processing and retrieving multiple types of data within a single, unified platform. However, we believe that this effort is necessary for understanding migraine, a complex neurosensory disorder involving interacting neuropeptide, inflammatory, vascular and network-level mechanisms. Furthermore, in the context of precision medicine, integrated biomarker panels are expected to guide therapeutic decisions, rather than single markers (15).

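### The primary objective is a biomarker panel reliably associated with response, but the plan neither measures how often a feature is reselected nor says how fold-specific subsets become the reported panel

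*Protocol article*

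**What the plan says.** Efficacy endpoint analyses: "The primary objective of the study is to identify a panel of biomarkers that is reliably associated with response to treatment". The criteria given there and under Model evaluation and validation (AUC, accuracy, balanced accuracy, predictive values and so on) judge models, not the membership of single features.

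Preprocessing and feature selection begins with a univariate screen: "Variables not showing evidence of association is going to be excluded from subsequent modelling". No threshold is given.

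Machine learning (ML) algorithms: "RF-derived feature-importance measures are going to be used to rank predictors according to their contribution to classification performance". After that, "a stricter feature-selection step based on RF importance rankings is going to be applied to identify a reduced and more informative feature subset", and "This reduced feature space will then be used to train and compare additional supervised machine-learning algorithms". No importance cut-off, panel size or repeat-selection requirement is stated.

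Model evaluation and validation: "All transformations, feature-selection procedures, class-balancing strategies and hyperparameter optimisation steps are going to be confined to the training folds". The same section says that "the final model specification depends on the observed data structure and on the retained feature set", and leaves the complete configuration to the results manuscript.

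The sections on sample size, preprocessing and limitations call the machine learning exploratory. The limitations section concedes a risk of spurious associations and leaves confirmation of stability to replication in other cohorts.

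**The concern.** The primary deliverable is a list of features, and the word that qualifies it is reliably. With selection inside the training folds, which is correct practice for estimating performance, five outer folds give five reduced sets. One reported panel then needs either a rule for combining those sets or a fresh ranking on all patients. Neither is described, and no step shows whether a feature would be chosen again if some patients were left out.

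Two things are at stake. Chance members could be published as reliable and carried into later validation cohorts. And the nested cross-validated performance, which is an average over models built on different subsets, could be read as the performance of the final panel, which that scheme never evaluates.

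**Working it through.** The plan states no figure for panel size, cut-off or stability, so there is none to reproduce. The check asks how much of a panel taken from one ranking would be real.

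**Inputs**
- Patients: 168 planned with a 6% loss (Sample size calculation). 168 × 0.94 = 157.9, so 158, split 79 v 79 (even split assumed).
- Number of candidate features p: not stated. The Strengths section mentions "genome-wide DNA methylation" and MRI features are added. Assumed 200, 1,000 and 10,000.
- Effect size d: not stated for responders v non-responders. Assumed 0.4 and 0.8. The planning figures in Sample size calculation (2.18 ± 1.91 v 5.85 ± 5.41) give d = 3.67/4.06 = 0.90 with the root-mean-square SD, or 3.67/5.41 = 0.68 with the larger SD. They compare migraine with healthy women at one gene, so they do not settle d here.
- Ten true features and a panel of ten, independent features, ranking by |t| as a stand-in for importance (all assumed).

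**Hand calculation.** A true feature has expected test statistic δ = d·√(n/4). With n = 158, √39.5 = 6.285, so δ = 2.51 at d = 0.4 and 5.03 at d = 0.8. The cut-off c for a panel of ten solves approximately

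10·Φ(δ − c) + (p − 10)·2·[1 − Φ(c)] = 10.

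| d | p | c | true members | false members |
|---|---|---|---|---|
| 0.4 | 200 | 2.30 | 5.9 | 4.1 |
| 0.4 | 1,000 | 2.75 | 4.1 | 5.9 |
| 0.4 | 10,000 | 3.35 | 2.0 | 8.0 |
| 0.8 | 200 | 3.16 | 9.7 | 0.3 |
| 0.8 | 1,000 | 3.44 | 9.4 | 0.6 |
| 0.8 | 10,000 | 3.85 | 8.8 | 1.2 |

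**Simulation of the same setting.** Separate runs gave true shares of 57–64%, 38–41% and 17–20% at d = 0.4, and 97–98%, 94% and 86–87% at d = 0.8, for p = 200, 1,000 and 10,000. This agrees with the hand calculation.

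**Closer to the planned pipeline.** Here an in-fold t-test screen at p < 0.05 (assumed; capped at the 500 smallest p-values) was followed by random-forest importance and a top-20 panel. There were 20 true markers, 158 patients and 5 folds repeated 3 times, with only three data sets per setting.

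| p | d | overlap of panels between folds | true/false in one full-data ranking | true/false kept if selected in ≥ 80% of training sets |
|---|---|---|---|---|
| 1,000 | 0.3 | 30% | 5.0 / 15.0 | 1.7 / 1.3 |
| 1,000 | 0.5 | 49% | 12.3 / 7.7 | 7.7 / 0.3 |
| 1,000 | 0.9 | 85% | 19.3 / 0.7 | 17.3 / 0 |
| 10,000 | 0.3 | 13% | 2.7 / 17.3 | 0.7 / 0 |
| 10,000 | 0.5 | 19% | 6.3 / 13.7 | 0.7 / 0 |
| 10,000 | 0.9 | 64% | 17.0 / 3.0 | 12.0 / 0 |

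Without any true marker (d = 0), a single ranking still returns 20 features. The 80% rule then kept on average 2.7 false members at p = 1,000 and 0.3 at p = 10,000.

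Selection frequency therefore separates stable from unstable members, but a hard 80% cut-off also discards many true ones when effects are small and features many.

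**The case against.** A reader might infer that the sections contradict each other, because one speaks of a single reduced feature space and the next makes selection fold-specific. The documents do not support that. The validation section covers all feature selection and governs the singular wording, so each algorithm would already work on its own fold's subset. What remains is a clarification of wording.

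A reader might also infer that the panel would be largely an accident of the sample. That depends on effect size and feature count, which the article does not give, and it fails for strong markers: at d = 0.8 or 0.9 most members are genuine. A choice such as 20 panel places for 10 true features would cap the true share at 50% by construction, which is why the panel of ten is used above.

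It is fair to add that the machine learning is labelled exploratory, that stability is named as unresolved, and that cut-offs and fold aggregation often sit in a full protocol or analysis plan, which are not shown here. This weakens the point without removing it. The caveats sit beside a primary objective that promises a reliable association, and they supply no measure of it. The article also ties the final specification to the observed data and to the results manuscript.

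The objection that an 80% threshold is arbitrary and can nearly empty the panel stands in full.

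**Conclusion.** The point holds in a limited form and should be addressed. The plan promises a reliable panel, takes it from importance rankings made within training folds, and has no step that measures repeat selection or converts fold-specific subsets into what is reported. The size of the problem is conditional: from a few per cent false members (10 true features, d = 0.8, 200 features) to about 80% (d = 0.4, 10,000 features). These figures rest on independent features, an even binary split, a chosen number of true features and, in the ten-feature calculation, |t| in place of forest importance. The random-forest runs used very few data sets and are indicative only. Separately from any simulation, the nested performance estimate belongs to the selection procedure and not to the final panel. Nothing here shows that the planned cross-validation leaks information or that the eventual panel will be wrong.

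**What to change.** - Repeat the nested cross-validation, for example 20 × 5 outer folds, which gives 100 outer training sets, and record which features are selected in each.
- Rank and report the panel by selection frequency, and publish the frequencies of all features.
- If a membership threshold is wanted, fix it before the response-stratified analysis. Status of the study says data processing for the stratified groups is still under way. 80% is only an example; for a discovery study, published frequencies without a hard cut-off may serve better.
- In Model evaluation and validation, state that cross-validated performance belongs to the selection procedure.
- In Machine learning (ML) algorithms, state that the reduced feature space is specific to each training fold.
- In Efficacy endpoint analyses, define a reliable association in terms of selection frequency.

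The cost is computing time and wording, with no new patients or measurements. The downside is a shorter and possibly empty panel under a strict threshold.
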